### Main effects, moderator and mediator analyses

Predictor analysis will focus especially on baseline IPV severity collected using the Danger Assessment Scale [40], scored 0–39, the Women’s Experience with Battering [41] scored 10–40 and alcohol dependence as identified by an AUDIT [22] score greater than 13. We will also explore other plausible confounders and predictors identified in the literature including: the partner’s drinking; patient’s use of illicit drugs, depression, PTSD, and history of sexual abuse/assault as child and/or adult. These covariates will be analyzed in the same manner as the longitudinal analysis of the primary measure. For secondary efficacy measures collected at baseline, 3, 6, and 12 months, HLM models will be implemented to compare the intervention and assessed control groups. Potential predictors will analyzed both as main effects and potential interaction effects with group assignments to assess for moderation.

And finally, should the intervention group demonstrate significant differences on IPV and drinking outcomes, we will assess for changes in women’s self-efficacy, readiness to change, and rates of engagement with informal and formal social support systems or treatment as significant mediators of the effect of the intervention on our primary outcomes.

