### Study hypotheses

● At-risk women who receive a brief motivational intervention – compared to an identically-assessed usual care group will have a reduction in days of heavy drinking (4 or more drinks/day) and incidents of IPV-assessed weekly for 3 months and by follow up interviews at 3, 6, and 12 months.

● Women’s self-efficacy, readiness to change, and rates of engagement with informal and formal social support systems will mediate the effect of the intervention on our primary outcomes.

● PTSD, a history of childhood sexual abuse, higher baseline severity of IPV and dependent drinking will moderate or reduce the effectiveness of the brief intervention.

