### Screening and subject recruitment

Data collection occurs approximately 10 hours per day, 6 days each week and ED providers are encouraged to make referrals of potentially-eligible patients during off hours. During data collection periods, Research Assistants (RAs) approach and attempt to screen all female patients in the ED using a psychosocial risk assessment (referred to as the Social Health Survey) that asks about IPV and risky drinking. Patients who indicated a risk for either IPV or risky drinking are asked to complete a formal assessment to determine study eligibility. The assessment includes the AUDIT [22] and CTS2S [23], is verbally administered by the RA to determine study eligibility of IPV and excessive drinking in the last 3 months – a score of 1 or more on the CTS2S and 4 or more on the AUDIT. For referrals outside of data collection hours and for women who are found to be potentially eligible but unable to stay in the ED, the Clinical Research Coordinator collects safe phone contact information to determine study eligibility and arranges an appointment for enrollment.

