### Statistical analysis

#### Analysis across all three groups

With a goal of identifying the impact of assessment alone, the outcomes below can be analyzed across all three groups: the Brief Intervention Group (BIG), the Assessed Control Group (ACG) and the no contact control group (NCCG) using a intent-to-treat analysis that includes all participants who complete randomization and enrollment procedures and provide baseline and/or at least one follow up data collection point. Analysis across all groups including the no contact control group (NCCG) will include eligibility assessment data (baseline) and 3-month interview data collected on CTS2S and the AUDIT assessments.

Alcohol outcome measures are the frequency of heavy drinking (4 or more drinks/day for women) collected at baseline in person and by phone interview at 3 months using one item on the AUDIT [22], to calculate the frequency of 4 or more drinks. The full AUDIT score (0–40) [22] and additional drinking data are collected using a calendar-based Timeline Followback [35] for the month (28 days) prior to the interview.

IPV outcome measures include the frequency of IPV incidents (emotional, physical, and sexual) collected at baseline and by phone interview at 3 months using the CTS2S [23], scored 0–96. These data are on a likert scale, capturing a range of frequencies of occurrence in the previous three months. IPV Severity is calculated as the number of IPV incidents classified as severe in the preceding 3 months measured using specific items on the CTS2S [23]. IPV type and severity is also captured through the Composite Abuse Scale [36], scored 0–150.

All of the above measures are collected at baseline and 3, 6, and 12 months for the Intervention and Assessed Control Group and at 3 months only for the Non-Assessed Control Group. So any comparison across all 3 groups is limited to 3 month outcomes.

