For the power analyses, we specified a Type-I error level (alpha-level) of 0.025 (splitting alpha between the two primary outcomes of heavy drinking days and IPV incidents). For heavy drinking outcomes, we derive a randomized sample size of 199 per group to achieve at least 80% power to detect a significant effect in the rate of change between groups with attrition/missing data of 30% during the first 12 weeks of treatment. For IPV primary outcomes, this size sample (199 per group) yields power of 93.7% for detecting a clinically significant result with 30% attrition/missing data across 12 weeks. Thus, a randomized sample of 240 subjects per group needed for the comparisons with the no contact control group is more than adequate for conducting the primary analyses comparing BIG to the Assessed Control groups.

For the analysis of intervention moderators, we assume that if the moderator variables are measured without error, we need a sample size of 55 to have 80% power to detect a medium effect with an alpha of 0.05. While demographic variables are measured without error, the baseline risk status variables have reliability indices closer to 0.90. Aiken and West [43] argue that the sample size required to reach a power of 80% with an alpha value of 0.05 is slightly more than doubled when reliabilities drop from 1.0 to 0.80. According to these standards, our sample size of 240 per group (accounting for 30% attrition) is more than sufficient to detect a medium effect size for a moderator.

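### Moderation by drinking is tested only through a split of the AUDIT at 13; adding the continuous score beside it would protect against missing graded moderation

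*Protocol article*

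**What the plan says.** The third hypothesis under Study hypotheses states that, among other factors, "higher baseline severity of IPV and dependent drinking will moderate or reduce the effectiveness of the brief intervention". Main effects, moderator and mediator analyses then names the predictors of most interest. The IPV measures are given as scores: "baseline IPV severity collected using the Danger Assessment Scale [40], scored 0–39", and the Women's Experience with Battering scale at 10–40. Drinking is given as a category: "alcohol dependence as identified by an AUDIT [22] score greater than 13". The use in the model is stated as "Potential predictors will analyzed both as main effects and potential interaction effects with group assignments to assess for moderation".

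The underlying score is already held. Screening and subject recruitment requires "a score of 1 or more on the CTS2S and 4 or more on the AUDIT" for eligibility, so each randomised woman has a baseline AUDIT of at least 4. Analysis across all three groups refers to "The full AUDIT score (0–40" as its range.

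For sizing, Power for analyses gives 55 women for 80% power to detect a medium moderator effect at alpha 0.05, discusses unreliability ("While demographic variables are measured without error, the baseline risk status variables have reliability indices closer to 0.90"), and concludes that 240 per group with 30% attrition is enough. The article gives neither a baseline AUDIT distribution nor an expected share above 13.

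**The concern.** A two-level split treats a woman scoring 4 like one scoring 13, and one scoring 14 like one scoring 40. If the intervention works progressively less well as drinking becomes more severe, the split measures that trend poorly: the interaction is estimated less precisely and missed more often. Moderation is one of the article's stated objectives. A null interaction on the split could be read as evidence that drinking severity does not alter the effect, when the test was merely weak. The score that would guard against this costs nothing further to obtain.

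**Working it through.** **Inputs.** From the article: n = 55, 80% power, alpha 0.05 and a medium effect; 240 per group with 30% attrition, so 240 × 0.70 = 168 per group and 336 in the two groups compared; cut at >13; entry floor 4; maximum 40. Assumed: medium means f² = 0.15; the moderator's shape and the AUDIT distribution are varied below. An ordinary linear model with one interaction term is used, as a simplification of the hierarchical models planned.

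**Step 1: reproduce the plan's figure.** The test is a 1-df F test with noncentrality f² × N. At N = 55 and f² = 0.15 (noncentrality 8.25) power is 80.5%. The stated 55 is reproduced.

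**Step 2: information kept by the split if moderation is linear in the score.** This is the squared correlation between the score and the >13 indicator. For a normal score it is φ(c)² / [p(1 − p)], where p is the share above the cut and c the matching normal quantile.

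| Share above 13 | Kept | Lost |
|---|---|---|
| 50% | 0.64 | 36% |
| 40% or 60% | 0.62 | 38% |
| 30% or 70% | 0.58 | 42% |
| 20% or 80% | 0.49 | 51% |
| 10% or 90% | 0.34 | 66% |

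For scores confined to 4–40, with roughly 15–70% of women above 13, normal and skewed (gamma) shapes mostly keep about 0.51–0.67, a loss of about a third to a half. Over all the skewed shapes tried, including ones with more than 90% of women above the cut, the loss ran from 27% to 79%.

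**Step 3: effect on power at 336 women.** On the full score, f² = 0.0235 gives 80% power. Multiplying by the share kept:

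- 0.0235 × 0.67 = 0.0157, power 63%
- 0.0235 × 0.51 = 0.0120, power 52%

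For a small interaction (f² = 0.02, assumed), power is 73% on the full score and 45–56% on the split.

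**Step 4: does the article's medium-effect statement survive?** Applying the same shares to f² = 0.15, the sample needed rises from 55 to about 81–105 (89–115 if the share kept is 0.64–0.50 and is applied to partial R² instead). Power at 336 stays above 99%. Halving the effect again for unreliability, in line with the doubling of sample size that the article cites for reliability 0.80, gives 0.15 × 0.51 / 2 = 0.038 and 0.15 × 0.67 / 2 = 0.050, with power of about 95% and 98%. The statement survives.

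**Step 5: reverse the assumption.** Simulation with 168 per arm, 3,000 runs, gamma scores limited to 4–40 and an interaction of 0.31 residual SD per moderator SD:

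| Mean (SD) AUDIT | Linear truth: score / split | Step at 13: score / split |
|---|---|---|
| 13 (7) | 76% / 57% | 60% / 78% |
| 16 (8) | 77% / 51% | 57% / 79% |
| 20 (8) | 76% / 38% | 41% / 79% |

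The last row has more than 70% of women above 13 and so lies outside the range in the main claim. Each coding wins when its own shape is true.

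**The case against.** The strongest reply is that the split tests what was hypothesised. The article speaks of dependent drinking, which is a category, and of higher severity for IPV, which is graded; a threshold for one and score ranges for the other follow that wording. This stands. The split is a legitimate test, Step 5 shows it is the stronger one if the effect changes at 13, and replacing it would remove the test of the hypothesis as worded.

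Three stronger readings are tempting and are not supported:

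- **That the trial does discard a third to a half of its information.** This is conditional on graded moderation and on an AUDIT distribution that the article does not report.
- **That the split undermines the moderator sizing.** Step 4 shows it does not.
- **That the split reduces the quoted reliability of about 0.90 to 0.51–0.67.** The article attaches that figure to baseline risk variables in general, not to the full AUDIT score. The squared correlation of a score with its own split can stand in for reliability only if the full score is the true moderator, which is the point in dispute.

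It can also be said that coding and sensitivity versions of moderators belong in a full analysis plan that is not shown. That limits the weight of the point, but the article does fix this coding explicitly and gives no reason for using the split alone.

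**Conclusion.** The point holds as a conditional loss of efficiency in a moderator analysis. With graded moderation, roughly 15–70% of women above 13 and 336 analysed, a test with 80% power on the full score has about 52–63% on the split. With a step exactly at 13, the split is preferable. Since the article does not establish which shape applies, relying on the split alone leaves the trial exposed to one of two plausible cases. Only interactions smaller than medium, and the precision of the estimate, are affected. The primary comparison, its sample size and its error rate are untouched. The label is a cheap improvement.

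**What to change.** In Main effects, moderator and mediator analyses, add the interaction of baseline AUDIT total with group as a pre-specified continuous moderator test for drinking, and report model-based intervention effects at stated scores on either side of 13. Keep the >13 by group contrast as the test of the dependent-drinking hypothesis as worded. State that a null result on the split alone will not be read as absence of moderation.

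The cost is a sentence or two of wording and one additional exploratory interaction test, with no new data, visits or participants. Non-linear terms guard against a wrong shape but use degrees of freedom: at f² = 0.0235 and 336 women, 80% power with one interaction term becomes about 71% with two and 64% with three if the extra terms explain nothing. Any such terms should therefore be few and named in advance.

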### Power for analyses

We conducted sample size estimation for analyses comparing among all three groups (intervention, assessed control, no contact control), with specific contrasts planned to compare (1) the intervention group to the no contact group, and (2) the assessed control group to the no contact group. Power analyses for these comparisons are based on mean differences at 3 months. With 120 randomized patients in the no contact control group, and 240 randomized to each comparison group, power (2-tailed; alpha = .05) is 80% to detect an effect size (Cohen’s d) of 0.33 with up to 30% attrition (84 vs. 168 patients for each comparison).

Additional power analyses were conducted for the comparisons of the Intervention and Assessed Control Group on the two primary outcome measures (reduction in heavy drinking; incidence of IPV). Based on previous studies [21,27], we considered a relative reduction of 2 or more (or approximately 35% reduction) heavy drinking episodes/month to be a clinically significant outcome. Blow [21] and D'Onofrio [27] suggest that rates of heavy drinking will be about 6.0 days/month (SD = 6.0) at baseline and end at about 3.5 days/month (SD = 5.0) at week 12 for interventions without a special motivational interviewing intervention that targets IPV and focuses on women only. For the power analysis given below we therefore specified a rate of change over weeks 4 to 12 in the brief intervention group (BIG) that will end with a 2 days/month improvement over the assessed control group (ie, 3.5 days per month for the assessed control group, 1.5 days/month for the brief intervention group).

In our calculations, we assume an autoregressive covariance structure with a within subject correlation of 0.6. The 0.6 assumption is comparable to what was seen with the Ball [42] study, where the average within subject correlation was 0.57. Converting the estimates above to weeks instead of months, assuming the effect seen in Ball [42] during the first month of treatment, we anticipate slope estimates per week during the second two months to be 0.109 and 0.046, respectively for the Assessed Control and BIG groups, with standard deviation over the second two months increasing proportionally from SD = 0 at week 4 to SD = 1.25 at week 12.

For the power analyses, we specified a Type-I error level (alpha-level) of 0.025 (splitting alpha between the two primary outcomes of heavy drinking days and IPV incidents). For heavy drinking outcomes, we derive a randomized sample size of 199 per group to achieve at least 80% power to detect a significant effect in the rate of change between groups with attrition/missing data of 30% during the first 12 weeks of treatment. For IPV primary outcomes, this size sample (199 per group) yields power of 93.7% for detecting a clinically significant result with 30% attrition/missing data across 12 weeks. Thus, a randomized sample of 240 subjects per group needed for the comparisons with the no contact control group is more than adequate for conducting the primary analyses comparing BIG to the Assessed Control groups.

For the analysis of intervention moderators, we assume that if the moderator variables are measured without error, we need a sample size of 55 to have 80% power to detect a medium effect with an alpha of 0.05. While demographic variables are measured without error, the baseline risk status variables have reliability indices closer to 0.90. Aiken and West [43] argue that the sample size required to reach a power of 80% with an alpha value of 0.05 is slightly more than doubled when reliabilities drop from 1.0 to 0.80. According to these standards, our sample size of 240 per group (accounting for 30% attrition) is more than sufficient to detect a medium effect size for a moderator.

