## Methods and design

### Setting, timeline, and general study design

This study is a longitudinal, randomized controlled trial, being conducted in two urban academic EDs staffed by emergency medicine faculty, residents, and nurse practitioners. These are the primary EDs and trauma units serving a 14-square mile area with mixed socioeconomic status and a population of over 200,000. Using a conservative prevalence range of 5-10% for risk of both IPV and problem drinking, we anticipated that recruitment from this medical venue would be adequate to achieve our target sample size based on the high patient volume (approximately 1,535 women subjects/year in the target age range). and the tendency for IPV victims and problem drinkers to receive their medical care from EDs The inclusion of two locations broadens our population and allows for greater generalizability.

Participants are randomized into one of three study groups using a 2:2:1 distribution: the intervention group (n = 240), the assessed control group (n = 240) and the no contact control group (n = 120). The assessed control group is interviewed at enrollment and at similar time points to the intervention group. The no contact control group is only assessed at 3-months, which enables us to determine the extent to which improvements over time in the intervention and assessed control groups maybe due to assessment reactivity.

This RCT began enrollment on January 18, 2011 and the target enrollment of 600 women was completed earlier than planned on November 6, 2013. Currently, we are in the middle of follow up data collection. Data collection will continue until approximately December 2014, the point at which all women in the intervention and assessed control group will have complete 12 month follow up measures.

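### The contrasts with the no contact group have about 69% power at d = 0.33 with 30% attrition, not the stated 80%; the effect detectable with 80% power is about 0.376

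*Protocol article*

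**What the plan says.** The article's Setting, timeline, and general study design section describes three groups: "Participants are randomized into one of three study groups using a 2:2:1 distribution", giving 240, 240 and 120 women.

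Power for analyses then treats the three-group comparisons separately from the primary one. It names "specific contrasts planned to compare (1) the intervention group to the no contact group, and (2) the assessed control group to the no contact group". It gives the basis of the calculation: "Power analyses for these comparisons are based on mean differences at 3 months". It gives the numbers: "With 120 randomized patients in the no contact control group, and 240 randomized to each comparison group", "power (2-tailed; alpha = .05) is 80" percent, for a Cohen's d "of 0.33 with up to 30% attrition (84 vs. 168 patients for each comparison").

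The same section later uses this result to justify the group size. After deriving 199 per group for the primary comparison, it concludes: "Thus, a randomized sample of 240 subjects per group needed for the comparisons with the no contact control group is more than adequate" for the primary analyses.

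**The concern.** The sentence is a complete power statement: test, sidedness, alpha, effect size, numbers analysed and power. It can be checked without the full protocol or an analysis plan, and the figures do not agree with one another.

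Two things depend on it. First, the article gives the contrasts with the no contact group as the reason for randomising 240 per group rather than 199. Second, assessed control against no contact is the trial's test of assessment reactivity, which is the purpose of the third arm. If that contrast shows no difference, readers will judge how reassuring this is by the stated power. They would take the chance of missing an effect of 0.33 to be one in five, when under the calculation as described it is nearly one in three.

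**Working it through.** **Inputs, all from Power for analyses.** Two-sided alpha .05; d = 0.33 (so SD = 1); 120 and 240 randomised; 30% attrition; difference in means at 3 months, with no covariate adjustment or correlation stated for this calculation.

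**Step 1: attrition.** 120 × 0.70 = 84 and 240 × 0.70 = 168. This matches "84 vs. 168 patients for each comparison", so the numbers analysed are right.

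**Step 2: power at d = 0.33.** The standard error of the standardised difference is √(1/84 + 1/168) = √0.01786 = 0.1336. The standardised signal is 0.33 / 0.1336 = 2.47. By the normal approximation, power = Φ(2.47 − 1.96) = Φ(0.51) = 69.5%. The noncentral t gives 69.1%. Pooling the error degrees of freedom over all three groups gives 69.3%.

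**Step 3: effect detectable with 80% power.** (1.960 + 0.842) × 0.1336 = 0.374 (normal), or 0.376 (noncentral t).

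**Step 4: can another reading reproduce the printed figures?** Noncentral t throughout:

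| Reading | Analysed | Power at d = 0.33 | d at 80% power |
|---|---|---|---|
| Two-sided .05 (as stated) | 84 vs 168 | 69.1% | 0.376 |
| One-sided .05 | 84 vs 168 | 79.3% | 0.333 |
| Two-sided .025 | 84 vs 168 | 58.5% | 0.414 |
| Two-sided .05, no attrition | 120 vs 240 | 83.7% | 0.314 |
| Two-sided .05, other two groups pooled | 84 vs 336 | 77.0% | 0.34 |

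Only the one-sided .05 test comes close to both 80% and 0.33, and it contradicts the stated sidedness. The pooled reading is not one of the named contrasts and still falls short.

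**Step 5: attrition at which the two-sided claim holds.** Power is 83.7% with no attrition, 80.2% at 9%, 79.7% at 10% and 69.1% at 30%. The claim therefore holds up to about 9%.

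**Step 6: size needed for d = 0.33.** The smaller group needs (1 + 1/2) × (1.960 + 0.842)² / 0.33² = 1.5 × 7.85 / 0.1089 ≈ 108.1 by the normal approximation and 108.8 by the t-test, so 109 vs 218 analysed. Dividing by 0.70 gives 156 no contact and 312 in each other group.

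**Step 7: what baseline adjustment would recover.** Adjusting for a baseline value with correlation r to the 3-month value multiplies the residual SD by √(1 − r²), so the effective effect is 0.33 / √(1 − r²). At 84 vs 168, two-sided .05:

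| Assumed r | Power at d = 0.33 |
|---|---|
| 0.30 | 73.2% |
| 0.40 | 76.6% |
| 0.45 | 78.7% |
| 0.48 | 80.1% |
| 0.50 | 81.1% |
| 0.60 | 86.8% |

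The break-even follows from 0.33 / √(1 − r²) = 0.376, which gives r ≈ 0.48.

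**The case against.** The strongest reply is that the planned analysis may be better than the power sentence. Analysis across all three groups proposes a generalized linear model of baseline and 3-month responses, and says that the eligibility AUDIT and CTS2S serve as baseline for all three groups. If r is about 0.48 or more, the 80% claim is recovered. The article uses a within-subject correlation of 0.6 elsewhere, and at that value power would be 87%.

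This stands as a possible remedy, but it does not rescue the sentence. The calculation is expressly based on 3-month means and gives no baseline to 3-month correlation. The 0.6 belongs to the weekly repeated measures in the intervention versus assessed control calculation, under an autoregressive structure, and the correlation over three months could well be lower.

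A second reply is that the attrition allowance is not at fault: at the stated 84 vs 168, a one-sided test gives the printed figures. That is the likeliest source of the error, although it is an inference. It explains the figures without making the sentence correct, because the sentence specifies a two-tailed test.

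A third reply concerns scope, and it is fair. The affected contrasts are at one time point and are not the primary comparison, which needs 199 per group by its own calculation and has 240. Enrolment is complete, so the larger numbers in step 6 only show the size of the gap. The article also states no rule for interpreting a null reactivity result, so the risk of misreading concerns how the result will be received, not a claim already made.

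**Conclusion.** The stated power is wrong for the test described. With 84 vs 168 analysed and two-sided alpha .05, power at d = 0.33 is 69% instead of 80%, a shortfall of about 11 percentage points, and the effect detectable with 80% power is 0.376. This rests on a two-sample comparison of 3-month means with a common SD, which is how the article describes the calculation. The result differs by less than half a percentage point between the normal, t and pooled-error versions.

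The error is confined to the two contrasts with the no contact group. It should be corrected before the reactivity result is interpreted, because the figure is given as the reason for the group size and determines how much weight a null result can bear.

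**What to change.** Make one of two changes to the sentence in Power for analyses.

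- **Restate the figure.** Say that 84 vs 168 analysed gives 80% power, two-sided alpha .05, for d of about 0.38, and 69% power for d = 0.33.
- **Change the basis.** State that the comparison is adjusted for the eligibility AUDIT or CTS2S score, and give the assumed baseline to 3-month correlation. The 0.33 claim needs about 0.48 or more; show power over a range such as 0.3 to 0.6 (73% to 87%).

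Relabelling the test as one-sided would make the numbers agree, but it would change the test to which the plan commits, so it is not the better repair.

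In either case, adjust the later sentence that rests the 240 per group on these contrasts, and word any null reactivity result to match the corrected detectable effect, preferably with its confidence interval. The cost is a sentence or two and, under the first option, a slightly less favourable detectable effect. No further patients or data collection are needed.

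### The fixed 0.025 split between the two primary outcomes is valid but needlessly conservative; Holm's procedure gains power at no cost

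*Protocol article*

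**What the plan says.** All references are to the protocol article.

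- *Primary outcomes collected by the interactive voice response system* numbers two separate primary outcomes: days of heavy drinking and number of IPV events.
- *Power for analyses* sets the error rate for their comparison: "we specified a Type-I error level (alpha-level) of 0.025 (splitting alpha between the two primary outcomes of heavy drinking days and IPV incidents".
- The same section powers each outcome on its own. For drinking, "we derive a randomized sample size of 199 per group to achieve at least 80% power to detect a significant effect", allowing for "attrition/missing data of 30% during the first 12 weeks of treatment". For IPV, "this size sample (199 per group) yields power of 93.7% for detecting a clinically significant result with 30% attrition/missing data across 12 weeks".
- It then says that "a randomized sample of 240 subjects per group needed for the comparisons with the no contact control group is more than adequate" for the primary comparison. *Setting, timeline, and general study design* reports that "the target enrollment of 600 women was completed earlier than planned", so 240 per group is the size of the actual trial.
- *Study hypotheses* puts both outcomes in one sentence: women given the intervention "will have a reduction in days of heavy drinking (4 or more drinks/day) and incidents of IPV-assessed weekly for 3 months".
- *Main effects, moderator and mediator analyses* makes the mediation analysis conditional: it follows "should the intervention group demonstrate significant differences on IPV and drinking outcomes".

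**The concern.** A fixed split tests each outcome at 0.025 whatever happens on the other. If one null hypothesis has already been rejected at 0.025, only one is left that could be falsely rejected. It can then be tested at the full 0.05 without raising the family-wise error. The fixed split leaves that alpha unused.

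The loss matters here because the trial is about two linked risks, and the mediation analysis depends on significant results for both. Suppose IPV gives p = 0.01 and drinking gives p = 0.04. Under the split only the IPV result counts, no effect on both can be claimed, and on a literal reading the mediation analysis is not run. Under Holm both are significant at an overall 5%, and the mediation analysis goes ahead.

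**Working it through.** **1. Inputs.** From *Power for analyses*: alpha 0.025 per outcome; power 80% for drinking (stated as at least 80%) and 93.7% for IPV, both at 199 randomised per group with 30% attrition; 240 per group randomised. Assumed, because not stated: two-sided tests for this comparison, and a correlation r between the two test statistics of 0 to 0.7.

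**2. The plan's own figure.** The printed inputs do not fix the 199. A plain week-12 comparison uses a difference of 2 days/month ÷ 4 = 0.5 days/week and SD 1.25, so d = 0.4. It needs 2 × (2.241 + 0.842)² / 0.4² ≈ 119 evaluable per group, and 119 / 0.70 = 170 randomised. Slope-based variants of the stated model range from about 48 to 445, which brackets 199. The IPV effect behind the 93.7% is not printed. I therefore take both stated powers at face value.

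**3. Error rate of the split.** 0.025 + 0.025 = 0.05, or 1 − 0.975² = 0.0494 if the outcomes are independent. The split is valid.

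**4. Noncentralities.** The critical values are z(0.9875) = 2.241 at alpha 0.025 and z(0.975) = 1.960 at alpha 0.05.

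- At 199 per group: drinking 2.241 + 0.842 = 3.083; IPV 2.241 + 1.530 = 3.771.
- At 240 per group, multiply by √(240/199) = 1.098: drinking 3.386; IPV 4.142.

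**5. Power for each outcome at 240 per group.**

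| Outcome | Tested at 0.025 | Tested at 0.05 |
|---|---|---|
| Drinking | Φ(3.386 − 2.241) = 0.874 | Φ(3.386 − 1.960) = 0.923 |
| IPV | Φ(4.142 − 2.241) = 0.971 | Φ(4.142 − 1.960) = 0.985 |

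**6. Holm at 240 per group, r = 0, by hand.** Drinking is rejected if it passes 0.025, or if it passes only 0.05 and IPV passes 0.025: 0.8738 + (0.9230 − 0.8738) × 0.9713 = 0.922. Both are rejected if both pass 0.05 and at least one passes 0.025: 0.8738 × 0.9854 + (0.9230 − 0.8738) × 0.9713 = 0.909. The split gives 0.8738 × 0.9713 = 0.849 for both.

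**7. Over the range of r (bivariate normal), 240 per group.**

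| r | Both, split | Both, Holm | Drinking, Holm | IPV, Holm |
|---|---|---|---|---|
| 0 | 84.9% | 90.9% | 92.2% | 98.4% |
| 0.3 | 85.4% | 91.1% | 92.0% | 98.1% |
| 0.5 | 85.9% | 91.3% | 92.0% | 97.9% |
| 0.7 | 86.6% | 91.6% | 91.9% | 97.6% |

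Under the split, drinking alone has 87.4% and IPV alone 97.1%, whatever r is.

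**8. The same at 199 per group, for reference.** Power for both is 0.80 × 0.937 = 75.0% (r = 0) to 78.5% (r = 0.7) under the split, and 83.7% to 85.5% under Holm.

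**The case against.** **The split is a legitimate choice.** The article describes two numbered primary outcomes, powers each one separately and divides alpha between them. That is a standard way to control family-wise error, and a conservative plan is not an incorrect one. This stands, so the point is an improvement and not an error. It is still more than taste, because Holm rejects everything that the split rejects and sometimes more.

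**Holm changes only some results.** With p = 0.03 and 0.04 neither procedure rejects anything. With p = 0.01 and 0.30 both reject only the first. This also stands. The gain is confined to results such as 0.01 and 0.04, where one p-value is at or below 0.025 and the other lies between 0.025 and 0.05.

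**The analysis plan may settle it.** The split is stated for the power calculations, the analysis sections do not repeat it, and a full plan may specify the procedure. The point therefore concerns only what the article fixes, which is 0.025 per outcome.

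**A stronger reading.** A reader might infer a contradiction: that the hypothesis and the mediation condition require success on both outcomes, while the split lets either one decide. The article does not support this. The conjunction in the hypothesis can simply list two outcomes that are tested separately. The mediation condition opens a follow-on analysis, which *Objectives* describes as exploratory, and may be stricter than the primary tests without conflicting with them. No rule for overall trial success is stated in either form.

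**Conclusion.** The fixed split is valid but leaves power unused. Label: free improvement. At 240 per group, Holm raises power for drinking from about 87% to 92%. Power for both outcomes rises from about 85-87% to 91-92%, a gain of 5 to 6 percentage points. IPV gains little, from about 97% to 98%. Family-wise error stays at 5%.

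These figures rest on the stated powers taken at face value, on reading at least 80% as exactly 80%, on the same 30% attrition at 240 as at 199, on two-sided tests, and on a correlation of 0 to 0.7. The size of the gain depends on these assumptions. That Holm never rejects less than the split does not.

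A reader might also infer a power shortfall from the 75-78% joint power that follows from the two stated figures. That belongs to 199 per group, which is not the trial that was enrolled. At 240 per group the joint power is already about 85-87% under the split, so there is no shortfall.

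**What to change.** Replace the fixed split with Holm at an overall two-sided 0.05: test the smaller of the two p-values at 0.025 and, if it is significant, the other at 0.05. State that each primary outcome supports its own claim, and that an effect on both is concluded only if both are rejected. Apply the same results to the condition for the mediation analysis. If joint power is reported, give it for 240 per group.

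The cost is a change of wording in the analysis plan, with no extra patients, visits or data. The article describes follow-up as still under way, to about December 2014. The rule should be fixed before the arms are compared on either outcome.
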